**Methods and analysis:**

The proposed randomized, double-blind clinical trial will investigate the effectiveness of PBM at reducing pain during the placement of the copper T 380 IUD. Seventy-two women will be randomly allocated to either an active PBM group (n = 36) or sham PBM control group (n = 36). In all participants, the standard IUD placement protocol will follow the guidelines of the Brazilian Ministry of Health. Pain will be assessed using the Visual Analog Scale (VAS) at multiple time points: during each step of insertion (Pozzi clamp, hysterometry, IUD placement) as well as 5 min, 15 min, 24 hours, and 48 hours post-procedure. The secondary outcomes will be analgesic use, anxiety levels (GAD-7), quality of life (WHOQOL-100), satisfaction with the procedure, and adverse effects. Ethics and dissemination. This clinical trial received approval from the Research Ethics Committee of the Mandaqui Hospital Complex (process: 7.367.867) and was registered in ClinicalTrials.gov (NCT06984796). Statistical analyses will be conducted using SPSS v24.0, with a significance level of 5%. Either parametric or nonparametric tests will be applied, depending on the data distribution. Kaplan-Meier curves will be used to assess time to pain resolution. The results will be disseminated through peer-reviewed publications.

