### Allocation (Sequence generation, allocation concealment mechanism, implementation)

A random sequence generator available online (https://www.sealedenvelope.com/) will be used to select the block randomization option with two treatments at a 1:1 ratio, resulting in equal numbers of patients in each group (n = 36 per group). As the total sample size is 72 patients, 12 blocks of six patients each will be established. Opaque envelopes will be sequentially numbered (1–72) and will contain the randomized group allocation. These envelopes will be sealed and stored securely until the IUD is placed. Only the designated researcher responsible for treatment will be aware of the assigned intervention. After opening, the envelope will be resealed and stored with the patient’s medical record, remaining concealed until the final statistical analysis. An individual not directly involved in the study will generate the random sequence and prepare the envelopes.

All participants will undergo the same IUD placement protocol performed by the same healthcare provider, as described in the “IUD Placement Protocol” section. Immediately after placement, the researcher in charge of applying PBM will retrieve and open an envelope, maintain the order of the remaining envelopes, and administer the assigned treatment (active or sham PBM). Only this researcher will be aware of the allocation.

The main investigator will oversee data storage (digital platforms) and organization. The statistician will be responsible for data analysis and will remain blinded to the interventions. The envelopes will also store participant records (patient history questionnaire, demographic data, risk factors, and statement of informed consent) and will be securely archived.

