#### Secondary outcomes.

Pain description – Free narrative reportNumber of analgesics taken – Paracetamol intake recorded from baseline to 48 hours after T 380 copper IUD placement.Anxiety – Assessed using the Generalized Anxiety Disorder 7 (GAD-7) questionnaire [15] 15 minutes after IUD placement.Quality of life – Measured using the WHOQOL-Pain instrument [16] from baseline to 48 hours after placement.Patient satisfaction – Assessed through close-ended questions [6] 15 minutes after placement.Time required for relief of abdominal discomfort (menstrual cramps) – Measured in days from baseline.Verification of successful placement – Investigated dichotomously (success/failure) from baseline to 48 hours after placement.Adverse effects – Including uterine perforation, IUD displacement, abdominal pain, increased vaginal bleeding, and allergic reactions. An open-ended question will be used for the participants to report adverse effects, followed by a list of potential impacts to help them recall any unreported symptoms.Side effects – including cramps, mild pain, light bleeding, and tongue numbness. An open-ended question will be asked first, followed by a list of potential side effects to improve recall.

*Primary outcome – Pain - Visual Analog Scale (VAS)*: Pain will be assessed using the Visual Analog Scale (VAS), as illustrated below. One end of the scale is marked “0”, corresponding to the absence of pain, and the other end is marked “10”, indicating unbearable pain. The same scale will be used for all participants. The same operator will always provide instructions for marking the scale. Pain scores will be recorded, and this assessment will be performed at all study visits, including during the IUD insertion phases (Pozzi, hysterometry, and IUD placement), at 5 and 15 minutes after placement, and at 24 and 48 hours after the procedure. The participants will be asked about spontaneous pain at three distinct moments during placement: pain during clamping with the Pozzi forceps, pain during hysterometry (uterine length measurement), and pain during the actual IUD placement. All participants will receive daily phone call reminders to ensure accurate recording of their outcomes [17].

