Patient satisfaction with T 380 copper IUD placement for contraception will be assessed 15 minutes after the procedure using guiding questions [6]. The assessment will include whether the placement experience was unpleasant, whether the patient would undergo the procedure again, and whether she would recommend it to a friend.

*Secondary outcome – Time required to relieve abdominal discomfort following PBM*: The time required to relieve abdominal discomfort following PBM will be recorded in hours, measured from the onset of cramps until complete pain resolution.

*Secondary outcome – Verification for IUD placement success*: IUD placement will be assessed as a binary outcome (success/failure).

*Secondary outcome – Adverse effects (uterine perforation, IUD displacement, abdominal pain, increased vaginal bleeding, and allergy)*: An open-ended question will be asked to elicit the patient’s free responses regarding adverse effects. The responses will then be listed nominally so that the patient may recall any impact that she may have forgotten to report.

*Secondary outcome – Side effects (cramps, mild pain, mild bleeding, tongue anesthesia)*: An open-ended question will be asked to enable the patient to freely describe any side effects. Effects will then be listed by name to help the patient recall any impact that she may have forgotten to report.

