### Statistical analysis

Statistical analysis will be performed using the Statistical Package for the Social Sciences (SPSS) version 24.0 or equivalent software package. The significance level will be set at 5% (p < 0.05) for all tests. Data normality will be determined using the Shapiro-Wilk test. Continuous variables will be reported as either the mean and standard deviation or the median and interquartile range, depending on the distribution of the data. Categorical variables will be expressed as absolute and relative frequencies. For comparisons between the experimental group (active PBM) and control group (sham PBM), the Mann-Whitney test will be used for continuous variables with non-normal distribution. When the expected minimum value is less than 5, categorical variables will be compared using either the chi-square test or Fisher’s exact test. The analysis of pain-related variables (intensity measured by the Visual Analog Scale [VAS]) at different time points (baseline, during placement, 5 and 15 minutes, and 24 hours after the procedure) will be conducted using the Friedman test. As the primary outcome will be measured repeatedly over time, the analysis will account for the within-subject correlation inherent to this repeated-measures design.

For the measures of anxiety (GAD-7), quality of life (WHOQOL-100), and satisfaction with the procedure, the Mann-Whitney test will be used to compare groups across assessment time points. The use of post-procedural analgesics will be compared between groups using repeated-measures analysis of variance (ANOVA). No interim analyses or stopping guidelines are planned due to the short duration of the trial and low risk.

Missing data will be assessed for frequency and pattern. In the event of missing values, the analyses will be performed using the available data, and the extent of missingness will be reported. If necessary, appropriate statistical methods will be applied depending on the nature and proportion of the missing data.

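### Time to relief of cramps has two incompatible definitions, the one timed from cramp onset gives women without cramps no value, and the Kaplan-Meier analysis promised in the abstract is absent from the statistical section

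*Protocol article*

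**What the plan says.** All references are to the protocol article.

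- *Secondary outcomes*, list: "Time required for relief of abdominal discomfort (menstrual cramps) – Measured in days from baseline".
- *Secondary outcomes*, detailed description of the same outcome: the time "will be recorded in hours, measured from the onset of cramps until complete pain resolution".
- *Abstract, Methods and analysis*: "Kaplan-Meier curves will be used to assess time to pain resolution". No time origin is given.
- *Statistical analysis*: this outcome is not named and Kaplan-Meier does not appear. For comparing the arms, "the Mann-Whitney test will be used for continuous variables with non-normal distribution". On missing values, "the analyses will be performed using the available data".
- *Secondary outcomes*, side effects: cramps are among the effects to be asked about, so the article does not assume that every woman has them.
- *Allocation*: "Immediately after placement, the researcher in charge of applying PBM will retrieve and open an envelope". The aim, Table 1 and Fig 3 nevertheless call the treatment preventive.

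**The concern.** There are three linked problems.

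1. The two definitions measure different things. Unless one is withdrawn, the choice could be made after the data are seen.
2. A duration that starts at cramp onset exists only for women who have cramps. If treatment can influence who has them, the arms compared are no longer the randomised arms, and a woman spared cramps altogether contributes nothing in favour of the treatment.
3. The method suited to a time-to-resolution outcome is named only in the abstract. The rule left in the statistical section needs a completed duration for every woman. One whose pain has not resolved when recording ends has only a lower bound, and leaving her out as missing would remove the longest durations.

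**Working it through.** **The definitions side by side.** For a woman with cramps:

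time from baseline to relief = (onset − baseline) + (resolution − onset).

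The list uses the left-hand side, in days. The description uses only the last term, in hours. They differ by the delay to onset, which varies between women, so converting units does not reconcile them. For a woman without cramps, onset is undefined and so is the last term. The article gives her no substitute value.

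The plan states no figure for this outcome, so there is none to reproduce. The calculations below rest on assumed inputs and show what restriction to cramping women can do.

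**Hand example (assumed).** Six sham women have cramps lasting 1, 2, 4, 8, 12 and 24 h: median (4 + 8)/2 = 6 h, mean 51/6 = 8.5 h. Suppose PBM prevents the three shortest and cuts the others by 10%, to 7.2, 10.8 and 21.6 h.

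- Cramping women only: median 10.8 h, mean 39.6/3 = 13.2 h, apparently worse than sham.
- All six, with no cramps scored 0 h: median (0 + 7.2)/2 = 3.6 h, mean 39.6/6 = 6.6 h, better than sham.

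**Closed form (assumed).** Sham durations are exponential with mean 10 h. PBM abolishes every cramp that would last under 5 h and changes no other.

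- Sham median: 10 × ln 2 = 6.9 h.
- PBM median among cramping women: 5 + 6.9 = 11.9 h, because the exponential is memoryless.
- Share of PBM women without a value: 1 − exp(−0.5) = 39%, about 14 of 36.
- Everyone counted: the median is 6.9 h in both arms, and the PBM mean is 15 × exp(−0.5) = 9.1 h against 10 h.

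**Simulation (assumed).** 36 women per arm (*Allocation*), two-sided Mann-Whitney at 5% (*Statistical analysis*), 4000 trials per row. Assumptions: 90% of sham women cramp; lognormal durations with median 6 h and log-SD 1; no censoring. Entries are the percentage of trials significant against / for PBM.

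| Cramps prevented by PBM | Cut in the rest | Cramping women only | All women, no cramps = 0 h |
|---|---|---|---|
| Shortest 10% | 10% | 4.4 / 1.0 | 0.8 / 5.9 |
| Shortest 30% | 10% | 30.4 / 0.1 | 0.7 / 16.6 |
| Shortest 30% | 30% | 5.4 / 1.0 | 0.4 / 40.6 |
| Shortest 50% | 10% | 73.3 / 0.0 | 2.5 / 50.5 |
| Shortest 50% | 20% | 55.1 / 0.0 | 1.7 / 60.5 |
| 30%, regardless of length | none | 1.9 / 2.7 | 1.5 / 52.2 |

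In the second row the medians among cramping women are 6.2 h (sham) and 8.2 h (PBM). Where prevention was unrelated to length, significant results against PBM among cramping women never exceeded 2.4%, which is within the 5%/2 = 2.5% expected by chance. There is no reversal there, but the prevention benefit disappears: power is 2.7% instead of 52.2%.

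**The case against.** Several stronger readings are tempting, and the article does not support them.

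- **That women without cramps are excluded.** No sentence says so, and an analysis plan could score them zero. What stands is that the definition as written gives them no value and the missing-data rule then works from what is available.
- **That cramps always follow randomisation.** The envelope is opened after placement, so cramps provoked by clamping, hysterometry or insertion may begin before allocation and before PBM. Having cramps would then be partly fixed beforehand and the bias smaller. The description of PBM as preventive points the other way; the article leaves this unreconciled.
- **That PBM would look harmful.** This needs prevention concentrated on short cramps and only modest shortening of the rest. It fades in the first and third rows of the table and is absent in the last.
- **That no between-arm test exists.** The generic Mann-Whitney rule would cover a duration in hours. With one common end of recording, unresolved women could even be given the worst rank, but the article states neither such a rule nor an end for this outcome.
- **That a scale in days can take only the values 0, 1 and 2.** The 48 h limit is stated for other outcomes, a 30-day visit exists, and nothing requires whole days.

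A log-rank test and a censoring rule are details usually left to an analysis plan, and their absence is not counted against the article. That argument does not cover the two published definitions, which cannot both hold, or an abstract that names an analysis missing from the article's own statistical section.

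**Conclusion.** The contradiction in unit and origin is explicit and needs correcting, as does the mismatch between the abstract and the statistical section. The lack of any value for a woman without cramps follows directly from the onset-based definition.

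The size of the resulting bias cannot be derived from the article. It depends on how many cramps begin after treatment, how many PBM prevents and which ones. The more general risk is loss of a real prevention benefit (power of about 3% instead of 52% in the assumed case of 30% prevented regardless of length). A reversed conclusion is possible only on the further assumption that mainly short cramps are prevented; significant apparent harm then ranged from about 4% to 73% of simulated trials in the rows shown.

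This is a secondary outcome. The primary pain analysis and N = 72 are not affected.

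**What to change.** 1. Use one definition in both places under *Secondary outcomes*: hours from a single origin common to all randomised women, for example the end of IUD placement, to complete and sustained pain resolution. The passages on when PBM is given must be reconciled before the origin is fixed. Sustained resolution is needed because a first report of no cramps would count a woman whose cramps begin later as already resolved.
2. Score women who never have cramps as time zero, and record explicitly that they had none so that they are not taken as missing. Check that the software keeps records with time zero.
3. Censor women with unresolved pain at the last recorded assessment (48 h if that is the end of recording), and state that end for this outcome.
4. Carry the abstract's Kaplan-Meier curves into *Statistical analysis*, with a log-rank test between the arms.

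The cost is wording, plus making sure that the clock time of resolution and the absence of cramps are captured. The description already calls for recording in hours. The article reports the trial as not yet recruiting, so the change can be made before any data exist.

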### Ethical aspects

This study ensures compliance with applicable ethical and regulatory guidelines. No modifications to the research protocol are planned; however, if any arise, they will be promptly communicated to all relevant parties, including investigators, the ethics committee (via an amendment submission), participants, and clinical trial registries. A trained researcher will obtain informed consent after providing the participants with detailed information about the objectives, procedures, risks, and benefits of the study, using a consent form written in clear, accessible language. No biological materials will be collected or stored. The collection, sharing, and storage of the participants’ personal information will follow strict data protection protocols to ensure confidentiality before, during, and after the trial. All data will be anonymized and securely stored to prevent unauthorized access. There are no financial or other conflicts of interest. Only the main investigator will have access to the final dataset. The researcher in charge is committed to disseminating the survey results to the participants, healthcare professionals, and the public through publications and presentations at conferences while respecting any previously agreed-upon publication restrictions.

### Statistical analysis

Statistical analysis will be performed using the Statistical Package for the Social Sciences (SPSS) version 24.0 or equivalent software package. The significance level will be set at 5% (p < 0.05) for all tests. Data normality will be determined using the Shapiro-Wilk test. Continuous variables will be reported as either the mean and standard deviation or the median and interquartile range, depending on the distribution of the data. Categorical variables will be expressed as absolute and relative frequencies. For comparisons between the experimental group (active PBM) and control group (sham PBM), the Mann-Whitney test will be used for continuous variables with non-normal distribution. When the expected minimum value is less than 5, categorical variables will be compared using either the chi-square test or Fisher’s exact test. The analysis of pain-related variables (intensity measured by the Visual Analog Scale [VAS]) at different time points (baseline, during placement, 5 and 15 minutes, and 24 hours after the procedure) will be conducted using the Friedman test. As the primary outcome will be measured repeatedly over time, the analysis will account for the within-subject correlation inherent to this repeated-measures design.

For the measures of anxiety (GAD-7), quality of life (WHOQOL-100), and satisfaction with the procedure, the Mann-Whitney test will be used to compare groups across assessment time points. The use of post-procedural analgesics will be compared between groups using repeated-measures analysis of variance (ANOVA). No interim analyses or stopping guidelines are planned due to the short duration of the trial and low risk.

Missing data will be assessed for frequency and pattern. In the event of missing values, the analyses will be performed using the available data, and the extent of missingness will be reported. If necessary, appropriate statistical methods will be applied depending on the nature and proportion of the missing data.

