### Outcome variables

#### Primary outcome.

Pain – Assessed using the Visual Analog Scale (VAS) at baseline, during the IUD placement phases (Pozzi, hysterometry, and IUD placement), 5 and 15 minutes after placement as well as 24 and 48 hours after the procedure.

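### The between-arm test and summary for VAS pain are left to a Shapiro-Wilk result, and Friedman, the one test named for VAS, does not compare active with sham

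*Protocol article*

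**What the plan says.** The Statistical analysis section of the protocol article contains these statements that bear on VAS:

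- A normality check: "Data normality will be determined using the Shapiro-Wilk test".
- A rule for summaries: continuous variables are "reported as either the mean and standard deviation or the median and interquartile range, depending on the distribution of the data".
- A rule for comparing active with sham PBM: "the Mann-Whitney test will be used for continuous variables with non-normal distribution". The test for normally distributed variables is not named.
- A sentence specific to VAS: its analysis over the listed time points "will be conducted using the Friedman test". No normality condition is attached.
- A general statement that "the analysis will account for the within-subject correlation inherent to this repeated-measures design".
- A level: "The significance level will be set at 5% (p < 0.05) for all tests".

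The abstract (Methods and analysis) gives the general rule: "Either parametric or nonparametric tests will be applied, depending on the data distribution".

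The Primary outcome section defines the outcome as VAS pain at baseline, at three insertion steps (Pozzi, hysterometry, placement), at 5 and 15 minutes, and at 24 and 48 hours. That is eight readings, with none singled out as primary.

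**The concern.** The design is a superiority trial of active against sham PBM, so its main claim is a between-arm difference in VAS. The only stated between-arm rule that can cover VAS is conditional on a normality result obtained after the data are in.

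VAS is bounded at 0 and 10 and is read repeatedly at points where pain will differ in level. With 36 women per arm, a normality test can fall on either side from one reading to the next. If the rule is applied at each reading, one insertion step could be reported as a difference in means and the next as a rank comparison with medians. These address different hypotheses and are not on a common scale. A reader could not say at which step PBM worked better, or by how much.

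**Working it through.** **No figure to reproduce.** The plan gives no VAS mean, SD or correlation and no number tied to the normality rule. The sample size of 72 is a separate matter.

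**Step 1: which rule compares VAS between arms?** The section fixes an unconditional Mann-Whitney for GAD-7, quality of life and satisfaction. For VAS it names Friedman. Friedman ranks each woman's own readings against each other and tests whether the readings differ over time. It has no group term, whether run on all women or within each arm. What remains for active versus sham is the general rule for continuous variables, which is gated by normality.

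**Step 2: Friedman under no PBM effect.** Simulation of 1000 trials, 36 per arm, eight readings. Assumed means were 1, 4, 5, 6, 3.5, 2, 1 and 0.5, SD 2.5 and correlation 0.5, with values rounded to 0.1 and clipped to 0–10. With no difference between arms, Friedman gave p < 0.05 in 100% of trials, because pain changes over the procedure. A significant Friedman result therefore says nothing about PBM.

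**Step 3: how often would a per-reading gate mix tests?** Assumed rule: Shapiro-Wilk at 5% in each arm; t-test if both arms pass, Mann-Whitney otherwise.

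- *Without assumed VAS values.* Take exactly normal, independent readings. Three insertion readings in two arms make six pre-tests. P(at least one rejects) = 1 − 0.95^6 = 1 − 0.735 = 0.265. A given reading goes to Mann-Whitney with probability 1 − 0.95^2 = 0.0975, and all three do so with probability 0.0975^3 = 0.0009. P(mix) = 0.265 − 0.001 = 0.264, about 26%.
- *Insertion readings with assumed VAS values.* 4000 trials per scenario, means 3.5, 4.5 and 5.5, SD 2.5, correlation 0.5, values limited to 0–10. Mixed tests occurred in 45% of trials with no effect, 68% with a 0.7 cm shift and 86% with a 1.2 cm shift.
- *All eight readings, set-up of Step 2.* Mixed tests occurred in 100% of trials with no effect and 98.5% with a 1.5-point shift. With no effect, the insertion readings passed as normal in 84% to 93% of trials. Baseline, 24 hours and 48 hours, which sit near zero under the assumed means, never passed.

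**Step 4: error rate and power at each reading (set-up of Step 2).**

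| Method | Rejection, no effect | Power, 1.5-point shift |
|---|---|---|
| Pre-test, then t or Mann-Whitney | 4.3–6.6% | 60–71% |
| t-test fixed | 4.5–6.5% | 56–71% |
| Mann-Whitney fixed | 3.9–6.5% | 60–70% |

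The Monte Carlo standard error at 5% is √(0.05 × 0.95 / 1000) = 0.7 percentage points. The three methods are practically indistinguishable.

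**The case against.** The strongest reply is that the plan does fix a test for VAS. Friedman is named without a normality condition, and within-subject correlation is to be accounted for, which does not fit a series of separate gated tests. This is correct as far as it goes: Shapiro-Wilk does not select the Friedman test. But Friedman cannot answer the superiority question, and the sentence on correlation names no between-arm comparison. The gated rule remains the only stated route from VAS to an active-versus-sham result.

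Three stronger readings are tempting, and the documents do not support them.

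- *That the plan prescribes a normality decision at each reading.* It does not state the unit. Per reading is a natural interpretation of a repeatedly read scale, but it is an inference.
- *That the normality gate is why no single PBM effect on VAS is estimated.* The main reasons are that Friedman has no group term and that eight readings are listed without a primary one. Deleting the gate alone would not supply the estimate.
- *That the gate inflates false positives.* The table above shows it does not, under the assumptions used.

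Two further points stand. First, a t-test and Mann-Whitney disagreed on p < 0.05 for at least one insertion reading in 13% of simulated trials at a 0.7 cm shift. Any two valid tests disagree sometimes, so that figure shows that the choice of test matters but does not measure damage done by the gate. Second, the unnamed parametric test and effect measure may be in the full protocol or a statistical analysis plan that is not shown, so their absence from the article is not the complaint. The complaint is about the rule that the article does state.

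**Conclusion.** The point holds in limited form. The stated plan leaves the between-arm test and the summary for the primary outcome to the observed distribution, and the one test named for VAS does not compare the arms. Both follow from the text without any simulation.

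The consequence for interpretation is conditional. If normality is judged at each reading, results on mixed scales are likely: about 26% of trials over the three insertion steps even with perfectly normal data, and 45% to 86% under the assumed bounded VAS values. These percentages are illustrative only. They rest on assumed means, SD, correlation, shifts, a t-test as the parametric option and a rejection rule applied by arm. Validity and power at each reading are little affected. This is a cheap and worthwhile improvement to the plan, not a threat to the error rate.

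**What to change.** In the abstract and the Statistical analysis section:

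- Remove the normality condition for between-arm comparisons of VAS.
- Replace Friedman as the primary analysis with one pre-specified between-arm method for all post-baseline VAS readings. An example is a repeated-measures mixed model with group, reading, group-by-reading and baseline VAS, with robust or bootstrap standard errors. List the 48-hour reading, which is part of the primary outcome but absent from the Friedman sentence.
- Report the active-minus-sham difference with a 95% CI at each reading.
- Give medians and quartiles as description at every reading, and Mann-Whitney as a sensitivity analysis at all readings alike.

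The cost is a few sentences and slightly more analysis work. The one real downside is reliance on mean differences for a bounded scale, which the robust or bootstrap errors and the rank-based sensitivity analysis are there to check. The article describes the trial as not yet recruiting, in which case the change can be made before any outcome data exist.

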## Materials and methods

A single-center, randomized, double-blind, controlled clinical trial with two parallel groups, designed as a superiority trial, will be conducted following the schedule of enrollment (Fig 1) and SPIRIT Statement (https://www.spirit-statement.org/) (S1 File).

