### Sample size calculation

The total sample size will be 72 participants. This number was calculated to provide an 80% power (α = 0.05) with an effect size of 0.14. The number of patients per group was determined using a sample size calculation with G*Power 3.1.9.7. The sample was calculated for two groups, and 8 measurements will be performed: at baseline, during the IUD insertion phases (Pozzi, hysterometry, and IUD placement), at 5 and 15 minutes after placement, and at 24 and 48 hours after the procedure.

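### The test named for the primary VAS outcome (Friedman) has no treatment-arm term, so it cannot compare PBM with sham, and its list of time points leaves out 48 hours

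*Protocol article*

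**What the plan says.** Materials and methods describes a "controlled clinical trial with two parallel groups, designed as a superiority trial". The question is therefore active PBM against sham.

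The Primary outcome section defines pain on the VAS at baseline, at the three insertion steps, and "5 and 15 minutes after placement as well as 24 and 48 hours after the procedure". That makes 1 + 3 + 2 + 2 = 8 scores. The Sample size calculation section agrees: "The sample was calculated for two groups, and 8 measurements will be performed".

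The Statistical analysis section covers this outcome in one sentence. It opens "The analysis of pain-related variables (intensity measured by the Visual Analog Scale [VAS]) at different time points" and continues "baseline, during placement, 5 and 15 minutes, and 24 hours after the procedure) will be conducted using the Friedman test". The next sentence promises that within-subject correlation will be taken into account, but names no model and no arm or arm-by-time term.

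Earlier, the same section gives a general rule for comparing the two arms: "the Mann-Whitney test will be used for continuous variables with non-normal distribution". It later names Mann-Whitney specifically for anxiety, quality of life and satisfaction, and a between-group repeated-measures ANOVA for analgesic use.

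**The concern.** VAS pain is the primary outcome, yet the test attached to it by name does not compare the arms. The Friedman null hypothesis is that scores do not differ between time points within a woman. Insertion is expected to hurt more than baseline, so the test should be significant in any such trial. A report following this sentence could present a very small p-value that says nothing about PBM, and a reader could take it as evidence of benefit.

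Separately, the list of times ends at 24 hours, so the last scheduled score of the primary outcome has no place in its stated analysis.

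**Working it through.** **1. The plan's own figure.** The stated inputs are 80% power, alpha 0.05, effect size 0.14, two groups, eight measurements and N = 72. Taking 0.14 as Cohen's f (the metric is not stated) and epsilon = 1, the G*Power forms are:

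- Interaction or within test: lambda = f² × N × m / (1 − rho), with 7 and 7(N − 2) degrees of freedom.
- Between test: lambda = f² × N × m / (1 + (m − 1) × rho), with 1 and N − 2 degrees of freedom.

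With rho = 0.5, the interaction or within test needs N = 48 and the between test N = 228. With rho = 0.25, the interaction or within test needs N = 70, and lambda at N = 72 is 0.0196 × 72 × 8 / 0.75 = 15.05, giving power 0.816. The correlation, epsilon, metric and choice of F test are not given, so 72 is neither reproduced nor refuted. The point does not depend on it. What matters is that the calculation refers to two groups and eight measurements.

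**2. What Friedman uses.** For n women and t times, Q = 12 / (n t (t + 1)) × Σ R_j² − 3 n (t + 1), where R_j is the sum over women of the within-woman rank at time j. Arm does not enter.

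**3. A hand example without noise.** Assume mean VAS of 1, 6, 4, 3, 2 at baseline, placement, 5 min, 15 min and 24 h. The ranks are 1, 5, 4, 3, 2.

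- No PBM effect, 72 women: rank sums 72, 360, 288, 216, 144. Σ R² = 285,120. Q = 285,120 / 180 − 1,296 = 288.
- PBM lowers every score after baseline by 1.5 in 36 women: active means 1, 4.5, 2.5, 1.5, 0.5, ranks 2, 5, 4, 3, 1. Pooled rank sums 108, 360, 288, 216, 108. Σ R² = 282,528. Q = 282,528 / 180 − 1,296 = 273.6.
- Per arm, each group of 36 has identical rankings, so Q = 36 × 4 = 144 in both arms, with or without the benefit.

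The 5% critical value on 4 degrees of freedom is 9.49. Every result is far beyond it, and a real benefit slightly lowers the pooled statistic.

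**4. With noise.** Assumptions: the same profile, SD 2, within-woman correlation 0.5, scores held to 0–10, 36 per arm, 2,000 trials. Mann-Whitney compares the arms on each woman's mean score.

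| Scenario | Friedman, pooled | Friedman, each arm | Mann-Whitney between arms |
|---|---|---|---|
| No PBM effect | 100% | 100% | 4.7% |
| 1.5-point benefit after baseline | 100% | 100% | 90.9% |

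A second run assumed SD 2.3, a profile peaking at insertion and a 2-point benefit, with Mann-Whitney at the peak. Friedman rejected in 100% of trials both without and with the benefit, Mann-Whitney in 5% and 94%.

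**5. Time points.** The abstract, Sample size calculation, Primary outcome and the detailed VAS description all include 48 hours. The Friedman list does not. Counting the three insertion steps separately, it covers 7 of the 8 scores.

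**The case against.** The strongest reply is that the plan does contain a between-arm test. VAS is a 0–10 score, so the general Mann-Whitney rule covers it whenever it is non-normal, and Friedman can be read as the within-woman complement. A reader might infer that VAS has no between-arm test anywhere in the plan. The document does not support that.

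The rule still does not repair the primary analysis. It is conditional on non-normality, and the section names no between-arm test for normally distributed VAS. It identifies no VAS time point or summary score, so it could yield a separate test at each time with none designated as primary. It does not deliver the within-subject handling that the section promises, and it does not match a calculation for two groups and eight measurements.

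Three other strong readings also fail:

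- **Friedman never reacts to PBM.** It can. With a flat profile (mean 5, SD 2.3, correlation 0.5, all assumed) and a 2-point effect starting only after baseline, pooled Friedman rejected in about 86% to 88% of trials. The reaction appears as a time effect and cannot be attributed to the arm.
- **Complete-row deletion contradicts the missing-data plan.** Friedman needs complete rows, which sits awkwardly with "the analyses will be performed using the available data". But the same paragraph allows other methods if needed, and no missingness rate is given.
- **The three insertion steps are merged into one.** The phrase for the placement period may simply be shorthand, since other sections list all three.

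**Conclusion.** The point stands and should be corrected before recruitment. The test attached by name to the primary outcome answers a different question from the trial's, and the 48-hour score is missing from its list. The first part follows from the form of the statistic and needs no assumption. That both arms and the pooled data will be significant regardless of PBM rests on pain rising at insertion. The 100%, 4.7% and 90.9% figures also rest on the assumed SD, correlation and profile. The omission of 48 hours is a plain disagreement between sections, whichever test is used.

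The claim goes no further. An arm comparison of VAS could still be made under the general rule, but the article does not say at which time, on what summary, or as the primary test.

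**What to change.** 1. **First reconcile the timing of PBM.** The Allocation section has PBM given directly after placement, while the aim in the Introduction, Table 1 and Figure 3 call it preventive. Which VAS scores count as post-treatment depends on this, so the passages must be reconciled before the model is fixed.
2. **Replace Friedman as the primary VAS analysis** with a linear mixed model for repeated measures (SPSS MIXED). Use the post-baseline scores, including 48 hours, with arm, time, arm-by-time and baseline VAS. An unstructured covariance over seven times has 7 × 8 / 2 = 28 parameters for 72 women, so name a simpler structure in advance as fallback if it does not converge.
3. **Name one primary time point or contrast**, since the article has none. Report the arm difference there with its 95% CI, with Mann-Whitney at that time as the rank-based sensitivity analysis.
4. **Keep Friedman, if wanted, only as a within-arm description**, and add 48 hours to its list.

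For orientation, an unadjusted comparison at one time with 36 per arm has 80% power for (1.960 + 0.842) × √(2/36) = 0.66 SD. That is about 1.3 points at an assumed SD of 2 and 1.5 points at 2.3.

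The cost is an amendment to the statistical section, with the chosen contrast also stated under the primary outcome. No new data are needed. The article lists recruitment as not yet started and already provides for notifying the ethics committee and the registry of changes.
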